## Product administration plan

Women will be instructed to insert one dose of gel, either Carraguard or placebo, vaginally every evening for the six days following the baseline visit. Women will be asked not to use other vaginal products, during the study period. Lubricated latex condoms with reservoir tips, and which are not lubricated with N-9, will be provided to limit any potential exposure to N-9. All participants will be informed that the study gel is to be used only vaginally, and that it is not designed for oral or rectal use.

## Follow-up visits

At follow-up visits the participant will be asked about the following:

- Occurrence of any medical problem or adverse event
- Sexual behavior and condom use
- Use of other vaginal products
- Study product use (day 7 only)
- Product acceptability (day 7 of second gel arm only)

At any time during the study, if a participant has questions, concerns, or unusual symptoms, she will be asked to return to the clinic promptly to meet with a study nurse or to have a clinical evaluation. If participants report for unscheduled visits, an evaluation of the existing problem will be undertaken and any necessary treatment will be provided. At all study visits, a rapid semen detection test will be conducted using a vaginal swab. If contaminated with semen, the visit will be rescheduled for 24-48 hours later.

Follow-up visit #1 (day 7):

The first follow-up visit (day 7) (for those assigned to a product arm, this visit follows seven days of product use) includes the following (See Tables 2 and 3):

- Interviewer-administered questionnaire concerning reproductive health, sexual practices, symptoms, experience using the product (Acceptability questionnaire). This is administered on day 7 of second gel arm only.
- Pelvic and colposcopic examinations
- Vaginal pool pH, Gram stain specimen collection and testing
- Sample for cervico-vaginal HIV viral load
- Clinician study form

Participants will be asked to bring all used and unused applicators to the clinic at each follow-up visit at which time they will be counted and logged. Women will be asked to return used applicators in individual sealable plastic bags, provided to the participants. Women will be asked if they tried to squeeze out all of the contents of the applicator, or if they chose not to use all of the product. At each Follow-up visit #1, the investigator will estimate study product and condom use based on a count of the used and remaining unused applicators and on an interview with the participant.

If participants have used study gel for less than 6 of the previous 7 days, they will be asked to use the study gel for up to 3 more days for a maximum of 6 days and return to the clinic at that time to complete the first follow-up visit.

During the pelvic examination and before the cervico-vaginal HIV viral load sample collection, a rapid semen detection test will be conducted using a vaginal swab. If contaminated with semen, the visit will be rescheduled for 24-48 hours later.

Follow-up visit #2 (day 14):

The second follow-up visit (day 14) (for those assigned to a product arm, this visit occurs7 days after the woman has stopped using the product), includes the following (See Tables 1-3):

- Pelvic examination
- Vaginal pool pH, and Gram stain specimen collection
- HPV testing
- Sample for cervico-vaginal HIV viral load
- Clinician study form

Women will then be asked to return to the clinic to begin the next study arm 3-5 days after the next menstrual period has ended.

Baseline visit:

The baseline visit will be the first visit of the new study arm. Women using depo provera will be placed on a regular 28 day schedule, so that day 0 will be approximately day 28 of the preceding cycle. In the event that a participant begins the study and she is unable to start her second or third study arms on time, we will allow the woman to start her next arm the following month. The Baseline visit, similar to the enrollment study visit, will include the following (See Tables 2 and 3):

- Interviewer-administered enrollment interview
- Collection of blood sample for plasma HIV viral load testing, HSV 1 and 2 antibody testing
- Baseline pelvic and colposcopic examinations
- Baseline sample collection for RTIs
- Baseline sample collection for cervico-vaginal HIV viral load
- Product administration (if a product arm)
- Second pelvic and colposcopic examinations (to assess acute effects of the product on the vaginal epithelium)
- Second sample collection for cervico-vaginal HIV viral load (to assess acute effects of the product on cervico-vaginal HIV viral load)
- Clinician study form

(The second examination and sample collection will not be conducted at the final study visit, day 28 of the third study arm).

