**Study plan**

Women will be screened for eligibility, which will include two screening visits, HIV, and tuberculosis testing, and an HIV clinical evaluation. If a woman has a husband or steady sex partner, he will need to come to the clinic for HIV testing to confirm that he is HIV-infected (and therefore not at risk for HIV infection related to the woman’s study participation) and to provide informed consent, because he may also be exposed to the study product, prior to her enrollment. Informed consent will be obtained. This study includes three study arms: Carraguard, placebo, and a no product arm. During the study, each woman will participate in each study arm, and she will be randomized to one of six study arm sequences (see section 5.5). At the enrollment visit, a pelvic examination will be conducted. During the examination, a baseline cervico-vaginal lavage (CVL) HIV sample and vaginal swab sample will be collected to quantify genital tract HIV, and a baseline colposcopic examination will be conducted to evaluate the mucosal epithelium. After the pelvic examination is conducted, the woman will be randomized to a study arm sequence. When receives a product, she will insert the gel vaginally as directed while still at the clinic. The participant and the research staff will be blinded regarding which gel the participant is using. Fifteen minutes after the product is inserted, a second pelvic examination will be conducted, 2 CVLs and vaginal swab samples will be collected, and a repeat colposcopic examination will be conducted to assess any acute effects of product exposure. If it is determined that one CVL is adequate to assess acute effects, only one CVL will be collected after the gel application at each baseline visit for the duration of the study. Participants who do not use a product will also undergo a second pelvic examination with CVL, vaginal swab and colposcopy at 15 minutes. During each study arm, the participant will use the designated product (or no product) for one week, beginning 3-5 days after the end of her menstrual period. She will have a total of two follow-up visits at day 7 and day 14 (1 and 8 days after discontinuing product use). Women and their partners will be counseled regarding the use of condoms and will be given condoms at no cost, to prevent transmission of different viral strains between partners. Women will be asked to return to the clinic for a pelvic examination with CVL and vaginal swab sample collection for HIV and colposcopy. On day 14 (~7 days after discontinuing product use), another pelvic examination with CVL and vaginal swab for HIV will be conducted. Women will then be asked to wait until 3-5 days after the end of the next menstrual cycle to return to clinic for the first visit in the next arm of their study arm sequence baseline study visit). Data from the baseline study visit will also be used for analysis of day 28 delayed effects or potential carry-over effects from the previous arm. A questionnaire regarding product use, acceptability, and adherence will be administered at the first follow-up visit (day 7) of each product arm. All women will participate in each study arm. The three study visits and data collection described above will be repeated for each of the 3 study arms.

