# Objectives

The objectives of the proposed study are to assess the effect of daily vaginal use of Carraguard gel by HIV-infected women on

- Safety
- Genital tract HIV shedding
- Product acceptability

Endpoints will be measured at the first follow-up visit (on study day 7), at the second follow-up visit (on study day 14, 7 days after discontinuing product use), and the next baseline visit (on study day 28, 21 days after discontinuing product use) and will be compared with the baseline assessment on day 0.

Acute effects of the product will be measured 15 minutes after the first application (enrollment visit).

Objective #1: To assess safety

Safety of daily product use will be determined by:

1. Symptoms of irritation
2. Effect on vaginal flora
3. Vaginal epithelial disruption as determined by naked eye inspection (and colposcopic inspection on day 7), according to established guidelines (16), and
4. Other adverse effects (which may include UTI or other unforeseen problems)

Objective #2: To assess effect on genital tract HIV viral load

Genital tract HIV will be measured using samples collected by CVL and vaginal swab, and viral load determinations will be performed using the COBAS AMPLICOR HIV-1 MONITOR v.1.5 Test Kit. In addition, levels of infectious virus will be determined using the multinuclear activation of a galactosidase indicator (MAGI) assay that identifies infectious cell-free HIV-1 in vaginal secretions.

Objective #3: To assess product acceptability

Women will be asked to complete an interview-administered questionnaire regarding acceptability of the product once each study arm at the first follow-up visit (day 7), after using the product daily for 7 days.

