## Data analysis

Objective 1: Product safety

Primary endpoints include epithelial disruption based upon colposcopic and naked-eye exams, vaginal flora disturbances, self-reported symptoms, and acquisition of RTIs. A random effects general linear model will be used which includes parameters for subject effects, treatment effects, period effects and first-order carry-over effects.

##

Objective 2: Genital shedding of HIV

Analyses will be based on a log transformation of the genital tract HIV viral load data, as suggested by preliminary data on genital tract HIV shedding from the CDC laboratory studies (unpublished). A random effects linear model will be used to analyze the data collected at the first follow-up visit, 7 days after daily product use. This model includes parameters for subject effects, treatment effects, period effects and first-order carry-over effects (defined as carry-over effects from the previous period). The subject effect will be treated as a random effect with a normal distribution. The random error term associated with a specific period and subject within a given sequence will be assumed to have a normal distribution with a compound symmetric (uniform) covariance structure. The chosen model assumes no sequence effect, which is reasonable given subjects are being randomized to each sequence. In addition, we assume no treatment by period interaction (i.e. the effect of genital tract HIV shedding for each treatment does not depend on the period it is administered), which seems to be a reasonable assumption for this study. Wash-out periods of three weeks between each treatment are expected to lessen the chances of observing a significant carryover effect. However, since little is known about the effects of these treatments on genital tract HIV viral load, the possibility of a carry-over effect will be tested. In the absence of carry-over effects, this will be dropped from the model and we can estimate the direct effect of the treatments on genital tract HIV viral load.

Objective 3: Product acceptability

Results from the Acceptability questionnaires will be tabulated, and associations between baseline demographic and sexual behavior characteristics and indicators of acceptability will be explored.

Weekly reports on enrollment and follow-up statistics will be distributed by Chiang Rai Health Club staff to the study team to assess trends.

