**Appendix 6: Table 3. Forms schedule**

| Study visit | Screen #1 | CRH referral visit | Screen #2 | Male  partner  visit | Enrollment | Follow-up #1 | Follow-up #2 | Baseline | Closing visit |
| --- | --- | --- | --- | --- | --- | --- | --- | --- | --- |
| Study day | ~ (-30) | ~ (-21) | ~ (-14) | Prior to enrollment | Day 0 | 7 | 14 | 0/28 | 28 of last arm |
| *Informed consent forms* |  |  |  |  | 3-5 days after menses |  |  |  |  |
| Screening Informed consent | X |  |  |  |  |  |  |  |  |
| Male informed consent |  |  | X |  |  |  |  |  |  |
| Enrollment Informed consent |  |  |  |  | X |  |  |  |  |
| *Study visit forms* |  |  |  |  |  |  |  |  |  |
| Eligibility checklist | X |  |  |  |  |  |  |  |  |
| Clinician screening form |  |  | X |  |  |  |  |  |  |
| CRH referral letter |  | X |  |  |  |  |  |  |  |
| CRH Assessment form |  | X |  |  |  |  |  |  |  |
| Male HIV test form |  |  | X |  |  |  |  |  |  |
| Comprehension test | X |  |  |  |  |  |  |  |  |
| Enrollment form |  |  |  |  | X |  |  |  |  |
| Enrollment interview |  |  |  |  | X |  |  |  |  |
| Clinician study form |  |  |  |  | X | X | X | X | X |
| Acceptability questionnaire |  |  |  |  |  | X* |  |  |  |
| Interview follow-up form |  |  |  |  |  | X | X | X | X |
| Closing form |  |  |  |  |  |  |  |  | X |
| *Additional forms* |  |  |  |  |  |  |  |  |  |
| Master checklist |  |  |  |  | X | X | X | X | X |
| Product distribution log |  |  |  |  | X |  |  | X |  |
| Medication log |  |  |  |  | X | X | X | X | X |
| Applicator usage log |  |  |  |  |  |  |  |  |  |
| Study gel interruption form |  |  |  |  |  |  |  |  |  |
| Adverse events form |  |  |  |  |  |  |  |  |  |
| Severe adverse events form |  |  |  |  |  |  |  |  |  |

*Only on Day 7 at end of second gel month

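### The protocol gives conflicting schedules for the acceptability questionnaire, and the one in the visit text and forms table leaves every first-gel rating to recall

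*Protocol*

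**What the plan says.** The protocol states the timing of the acceptability questionnaire in five places.

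- Study summary, Study plan: a questionnaire on use, acceptability and adherence "will be administered at the first follow-up visit (day 7) of each product arm".
- Objectives, Objective #3: women are asked about "acceptability of the product once each study arm at the first follow-up visit (day 7"), after a week of daily use.
- Follow-up visits, list of topics: "Product acceptability (day 7 of second gel arm only").
- Follow-up visits, Follow-up visit #1: "This is administered on day 7 of second gel arm only".
- Appendix 6, Table 3, footnote to the questionnaire's entry: "Only on Day 7 at end of second gel month".

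Under Data analysis, Objective 3, the results are to be tabulated, and "associations between baseline demographic and sexual behavior characteristics and indicators of acceptability will be explored". No comparison of Carraguard with placebo on acceptability is stated there. The questionnaire is named in the list of study forms, but its items are not shown.

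**The concern.** Acceptability is one of the trial's three objectives, and the protocol gives incompatible instructions on when to measure it. Two places promise a rating for each arm. Three places, including the visit list and forms table that staff would be expected to work from, allow one rating per woman. If staff follow the visit text, the data promised in the objectives will not exist, and no analysis plan can recover a rating that was never taken.

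Two things are at stake. The first is how soon after use each gel is rated. A single interview after the second gel records the first gel only from memory, if at all. The protocol describes the placebo as matching Carraguard in look, feel, smell and taste, which makes it harder to tell the two gels apart in retrospect. The second is who supplies data. A woman who stops before completing her second gel gives no questionnaire, and if dislike of a gel contributes to stopping, the missing answers bear directly on the objective.

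**Working it through.** The protocol states no figure for this objective, so there is none to reproduce. The check compares the schedules and then follows the six sequences.

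**Inputs.** 60 women (Study population); equal numbers per sequence (Sample size), hence 60/6 = 10 each; the sequences as listed under Study arm sequences, with A = Carraguard, B = placebo, C = no product.

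**Questionnaires implied by each text, with all 60 women completing**

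- Each product arm (Study plan): 60 x 2 = 120.
- Each study arm, read literally (Objective #3): 60 x 3 = 180. This would include the no-product arm, where there is nothing to rate. The same sentence refers to a week of product use, so both gel arms is the sensible reading, again 120.
- Second gel arm only (Follow-up visits; Table 3 footnote): 60 x 1 = 60.

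**Second-gel-only schedule by sequence**

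| Sequence | First gel (period) | Second gel (period) | Cycles between | Women |
|---|---|---|---|---|
| A-B-C | A (1) | B (2) | 1 | 10 |
| A-C-B | A (1) | B (3) | 2 | 10 |
| B-A-C | B (1) | A (2) | 1 | 10 |
| B-C-A | B (1) | A (3) | 2 | 10 |
| C-B-A | B (2) | A (3) | 1 | 10 |
| C-A-B | A (2) | B (3) | 1 | 10 |

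- Questioned just after Carraguard: B-A-C, B-C-A, C-B-A = 30 women, all of whom used placebo first.
- Questioned just after placebo: A-B-C, A-C-B, C-A-B = 30 women, all of whom used Carraguard first.
- Recall of the first gel spans one cycle in four sequences (40 women) and two cycles in A-C-B and B-C-A (20 women). The Baseline visit text lets a delayed arm start a month later, which would lengthen this.
- The second gel falls in the third period in four sequences. So 40 of 60 women must stay until day 7 of their last arm to give any acceptability questionnaire.

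**Illustration of precision.** Suppose someone compared the two gels using only ratings taken at the end of use, on a continuous score with standard deviation s and within-woman correlation r. Both the score type and r are assumptions.

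- 30 against 30 women: variance = 2s²/30.
- 60 pairs: variance = 2s²(1 − r)/60.
- Ratio = 2/(1 − r): 2 at r = 0, and 2/0.5 = 4 at r = 0.5.

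For two-sided 0.05 and 80% power (also assumed), the multiplier is 1.960 + 0.842 = 2.802.

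- Between women: 2.802 x √(2/30) = 0.72 SD.
- 60 pairs: 2.802 x √(2(1 − r)/60) = 0.51, 0.43, 0.36 and 0.28 SD for r = 0, 0.3, 0.5 and 0.7.

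**The case against.** The second-gel restriction appears three times, with an explicit footnote, so it looks deliberate. One interview after both gels have been used is a reasonable design, and correcting the Study plan and Objective #3 instead would also remove the contradiction. This stands: the protocol does not show that a single interview is an error, and which schedule to keep is partly a matter of judgement.

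A reader might infer that the second-gel schedule makes a within-woman comparison of Carraguard and placebo impossible. The protocol does not support that. By then every woman who reaches the interview has been through both gels, the items are not shown, and they could ask about both gels or about preference. What is lost is a rating of the first gel at the end of its use.

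Nor is a planned test damaged. The Data analysis section plans tabulation and exploration of associations, and the power calculation concerns HIV shedding. The precision figures therefore describe a contrast that the protocol does not state, and they assume 60 complete pairs. That is optimistic, since 60 are enrolled partly to cover losses and women who start antiretroviral therapy, whose data are to be analysed separately.

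Finally, the first gel arm does yield some related information. Product use and applicator counts are recorded at each day 7 visit, and a follow-up interview form is scheduled. These record use; they do not replace the acceptability questionnaire.

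**Conclusion.** The contradiction is established from the operative text and needs to be resolved. The Study plan and Objective #3 call for a questionnaire per arm, while the Follow-up visits section and the Table 3 footnote allow one per woman.

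If the visit text is followed, there are at most 60 questionnaires instead of 120. Carraguard is rated at the end of use by 30 women rather than up to 60, all of them after placebo. First-gel answers depend on recall over one or two cycles, and women who leave before completing a second gel contribute none. These counts assume 10 women per sequence and full retention.

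The result is a weaker basis for comparing the gels within a woman, not the loss of that comparison. The variance ratio of 2/(1 − r) is illustrative: it rests on an assumed r, a continuous score and an analysis the protocol does not state. The objective is descriptive and the shedding hypotheses are unaffected, so this is a point to correct rather than a threat to the trial's main conclusions.

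**What to change.** Reconcile the texts by giving the questionnaire at day 7 of both gel arms and not in the no-product arm.

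- Amend both statements under Follow-up visits and the footnote to Table 3.
- In Objective #3, replace the reference to each study arm with each gel arm.
- Keep any question on which gel is preferred for the second gel arm.
- Tabulate acceptability by gel, using each woman's paired answers where she has both and keeping the single answer of a woman who completes only one gel.

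The cost is one more short interview per woman at a visit that already takes place, plus the edits to the visit text and forms schedule. If the sponsor prefers a single interview, the Study plan and Objective #3 should be changed to say so. The protocol should then state that first-gel answers are recalled and that women without a second gel contribute no questionnaire.

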The definition of noncompliance is less than 6 days of study gel use reported at the first follow-up (7 day ) visit. Women who do not meet this criterion will be asked to use gel for up to 3 more days, for a maximum of 6 days. For the analysis, women who use study gel 6 of 9 days or more will be included in the per protocol analysis and those who do not meet this criterion will be included in the intention to treat analysis.

We will have a statistician review the mucosal safety data after the first 25 women have completed the first gel use arm. We will look at the differences in epithelial disruption (includes abrasions, ulcers, and fissures) from baseline to the first follow-up visit (day 7) and compare these differences between the 3 study arms. We will stop enrollment in the study and form a DMC to review the data if there is a difference between groups that is significant at the p<0.001 level, a standard stopping rule for this type of trial (Reference: Geller, N and Pocock, S. Interim Analyses in Randomized Clinical trials: Ramifications and Guidelines for Practitioners. Biometrics 43 1987 213-223).

Study participants will be provided with information regarding how to contact the Chiang Rai Health Center for study results and their blinding code when results are available. Results of the final analysis will be presented to the Chiang Rai Advisory Committee, and at local and international scientific meetings. We also plan to publish the results in the international scientific literature.

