# Product interruption criteria

Application of the study product will be interrupted in the following circumstances:

- Pregnancy
- Genital or other major surgery
- Medical condition incompatible with the study protocol or visit schedule
- SAE related to the investigational product
- Consent withdrawn
- Missed follow-up visit. However, at the investigators’ discretion, a participant may resume study participation (after her next menstrual period if menstruating)
- Lack of compliance

If an emergency, such as anaphylactic shock occurs, arises and it is necessary to unblind the product used by a particular participant, four individuals will have access to the randomization scheme, and can be reached both at work and at home, 24 hours a day, at the following telephone numbers:

[name] (NY): work: [contact] home: [contact]

[name] (NY): work: [contact] home: [contact]

[name] (NY): work: [contact] home: [contact]

[name] (Bangkok): work: [name] home: [name] [contact]

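### A woman with fewer than 6 days of gel use meets both an extend rule and an interrupt rule, and the extension appears to move her day-7 examination to day 8-10, in gel arms only

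*Protocol*

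**What the plan says.** Three sections of the protocol deal with a woman who has used too little gel.

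- **Data analysis** sets the threshold: "The definition of noncompliance is less than 6 days of study gel use reported at the first follow-up (7 day ) visit". It continues: "Women who do not meet this criterion will be asked to use gel for up to 3 more days, for a maximum of 6 days". Women who reach at least 6 days of use out of 9 enter the per-protocol analysis.
- **Follow-up visits** (day 7) repeats the instruction as a visit procedure, with the same trigger of fewer than 6 days in the week just ended. Such a woman is "asked to use the study gel for up to 3 more days for a maximum of 6 days and return to the clinic". The purpose of coming back is to finish the visit already due. That visit contains the pelvic and colposcopic examinations and the viral-load sample.
- **Product interruption criteria** opens with "Application of the study product will be interrupted in the following circumstances" and includes in its list "Lack of compliance". It gives no threshold, no cross-reference and no exception for a woman who is being extended.

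Objectives and Data analysis treat the first follow-up visit as study day 7. Data analysis also plans an interim review, after 25 women have completed the first gel arm, of the change in epithelial disruption from baseline to that visit, compared between all three arms. A difference at p<0.001 stops enrollment and leads to a DMC being formed.

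**The concern.** Clinic staff who find a woman below 6 days of use have two instructions that point in opposite directions: continue gel, or interrupt it. Nothing says which prevails. The trigger is the number of days used, so a woman who stopped because of irritation is handled in the same way as one who forgot.

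Timing is the second issue. If the first follow-up visit is completed only after the extra doses, the colposcopy at that visit moves with it. By Table 2 this is the only colposcopy scheduled between the 15-minute check and the next baseline. A woman in the no-product arm has no gel days to make up, so her examination stays on day 7. Epithelial disruption and self-reported symptoms are primary safety endpoints, and the comparison with no product would mix examination days in two arms with a fixed day in the third.

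**Working it through.** **1. The two rules side by side**

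| Section | Condition | Instruction |
|---|---|---|
| Follow-up visits; Data analysis | fewer than 6 days of use at the day-7 visit (called noncompliance in Data analysis) | up to 3 more days of gel |
| Product interruption criteria | lack of compliance, not defined there | product interrupted |

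The only definition of noncompliance in the protocol is the first row's condition. Read with that definition, the second row covers the same woman.

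**2. Dosing days.** The first dose is inserted in clinic on day 0 (Enrollment visit). One dose follows on each of the next six evenings (Product administration plan). That is 7 doses, on days 0 to 6. An unextended woman is therefore seen 7 − 6 = 1 day and 14 − 6 = 8 days after her last dose, which matches one of the two statements in the Study plan.

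**3. Effect of the extension.** Let u be the days used by day 7. I read the maximum of 6 as a total. I also assume that extra doses start on day 7 and that she returns the day after the last one.

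- Extra days: k = min(3, 6 − u)
- Examination day: 7 + k
- Last dose: day 6 + k
- Gap to a visit held on day 14: 14 − (6 + k) = 8 − k

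| Days used (u) | Extra days (k) | Total | Examination day | Last dose to day 14 |
|---|---|---|---|---|
| 5 | 1 | 6 | 8 | 7 days |
| 4 | 2 | 6 | 9 | 6 days |
| 3 | 3 | 6 | 10 | 5 days |
| 2 | 3 | 5 | 10 | 5 days |
| 1 | 3 | 4 | 10 | 5 days |

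With 1 or 2 days of use, the extension cannot reach 6 days, so she has further doses and still misses the per-protocol criterion by the time of the visit. Zero days should not normally occur, because the first dose is given in clinic.

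**4. Day-14 anchor.** The Study plan gives 8 days after stopping in one place and about 7 in another. Objectives, Overview and Follow-up visits give 7. If the visit is instead counted as 7 days after the last dose, an extended woman is seen on day 6 + k + 7 = 13 + k, that is day 14, 15 or 16.

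**5. How many examinations.** There are 60 × 2 = 120 gel periods and 60 no-product periods. The protocol gives no expected rate of under-use. If 10% to 20% of gel periods fell below 6 days (my assumption), 12 to 24 examinations would move, against none in the no-product periods.

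**6. Is the examination really deferred?** The text does not say so outright. Its wording, that she returns to complete the visit, points that way. The specimen plan is consistent with one day-7 collection per arm: 3 × (1 baseline + 2 acute + 1 day 7 + 1 day 14) + 1 closing = 16 lavages, the stated total. This is weak support, because 16 is a nominal count that leaves out repeat collections after a semen-positive visit.

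**The case against.** The best reply is that the interruption list means something broader. The definition of noncompliance sits in Data analysis and leads to the per-protocol criterion. The interruption item may mean general failure to follow the protocol, for which Partner HIV testing and informed consent already allows discretionary discontinuation. It may also be meant to apply only once the make-up days have failed. Either reading is possible. Neither is written down, so the conflict stands as text, though as something to clarify and not as proof that the sponsor intended both.

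Five stronger conclusions are tempting, and the documents do not support them:

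- *Extended women are over-exposed.* They are capped at 6 days, against 7 scheduled doses. The extension makes up missed doses.
- *Symptoms go unasked.* Follow-up visits already has women asked about medical problems and adverse events and, on day 7, about product use. Table 3 schedules the follow-up interview form at this visit. What is missing is the reason for missed doses and a stated order of events.
- *Day 7 is the only safety check.* There is a 15-minute examination after the first dose and a pelvic examination on day 14. The narrower statement about colposcopy is the one that holds.
- *A lesion present on day 7 is never recorded that day.* This follows only if the examination is deferred, which is inferred.
- *Practice will vary between sites.* There is one site.

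The extension applies alike to both blinded gels, so the rule itself does not affect the Carraguard-placebo comparison. Semen-test rescheduling applies in every arm and neither explains nor offsets the shift seen only in gel arms.

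**Conclusion.** The point holds, and should be fixed. As written, a woman below 6 days of gel use meets an instruction to continue and an instruction to interrupt. That needs no numerical assumption, only that the protocol's single definition of noncompliance applies where the term is used without one.

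The timing point holds in a smaller form. On the most natural reading, the examination moves by 1 to 3 days in gel arms only, while the analysis labels it day 7 in all three arms, including in the interim review. The exposed contrast is gel against no product. Day 10 is the extreme and arises only with 3 or fewer days of use; a woman who used gel on 5 days moves by one day. The day-14 interval is stated inconsistently (7 or 8 days after stopping), and an extension shortens it to 7, 6 or 5 days if the visit keeps its date. How many women are affected cannot be derived from the protocol.

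**What to change.** - Reconcile Follow-up visits, Data analysis and Product interruption criteria so that one stated rule governs a woman below 6 days of use. Which rule that should be is a clinical decision for the sponsor and is not proposed here.
- State in Follow-up visits whether the pelvic and colposcopic examination takes place at the first attendance or on return.
- Record the symptom and adverse-event answers and the reason for missed doses at the first attendance, using the interview already scheduled.
- Record the actual examination day and the days since last dose, so that the three-arm safety comparison, including the interim review, can account for them.
- State whether day 14 is counted from day 0 or from the last dose, and use the same interval in the Study plan, Objectives, Overview and Follow-up visits.

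The cost is protocol wording and one form field. No extra examination is needed.
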